***Study participants***

Individuals aged 45 years and older who consult their GP with peripheral joint pain or OA (from a designated set of pre-determined Read codes) will form the sampling base for the trial.

*Inclusion criteria:*

- Aged 45 years and over
- Registered with the participating GP practices during the specified study period of that practice
- Read-coded peripheral joint pain or OA consultation within the specified study period (termed the “index consultation”; may be first, new episode, or ongoing consultation)
- Provided full written informed consent to study participation and to further contact

*Exclusion criteria:*

- Patients who are under active care for or who have a diagnosis of depression and/or an anxiety disorder in the past 12 months
- Vulnerable patients, including any patients on the Quality and Outcomes Framework mental health register, or those who have a diagnosis of dementia or a terminal illness
- Patients who reside in a nursing home
- Red flag pathology – recent trauma associated with significant injury; acute, red, hot swollen joint
- Inflammatory arthropathy, crystal disease, spondyloarthropathy and polymyalgia rheumatica

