***Mailing procedure***

An illustrated summary of the mailing procedure is provided in Figure 2. All eligible patients will be sent a study pack as outlined above. Those who do not respond within 2 weeks will be contacted again with a postcard reminder. At 4 weeks those who have not responded will be sent a second study pack and reminder letter. At baseline, patients who have still not responded at 8 weeks will be recorded as non-responders and will not be contacted again at any point in the study and their medical records will not be accessed. Participants who respond to the questionnaire but who do not consent to further contact, which will be specified on the consent form as being in 3, 6 and 12 months time, will also be recorded in the database as a non-consenting responder, ensuring that we do not contact them again in the future (this may occur by returning a completed or blank questionnaire or verbally by telephone conversation).

*Follow-up*

Participants who return a questionnaire and consent to participate at baseline will be sent a follow-up questionnaire at 3, 6 and 12 months following their index consultation. In order to maximise participation a short questionnaire, including only minimal data collection items (outlined below), will be sent to participants who have not responded to the full postal questionnaire at 6 weeks. At 6 and 12 month follow-up points an additional telephone call will be used at 8 weeks (for those participants who provided a telephone number in their baseline questionnaire) to attempt to contact non-responders in order to get information on their pain intensity at that time. Three telephone call attempts will be made to contact each participant. The mailing procedure is outline in Figure 2.

**Figure 2:** Mailing procedure

[figure not shown]

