## Sample size

In order to use the information recorded at all the time points we have considered the sample size needed to estimate the time-averaged difference in the pain response between the two arms. Diggle et al (2002) give the number of subjects needed per arm as M=2(z_α_ + z_β_)^2^{1+ (n-1)ρ}/(nΔ^2^), using a significance level of α, power 1-β, Δ= smallest meaningful difference in standard deviation units, n=number of repeated measures [63]. Given that the mean difference is expected to be zero at baseline, we will think of the effect size as an average of 0.2 over the three follow up time points. Using ρ=0.5 as an estimate of the autocorrelation, n=3, Δ=0.2, α=0.05, β=0.10, gives 350 per arm. To adjust for the clustering of the practices we modify this figure by the design effect (1+(m-1)*icc) for an average cluster size m. Using an icc=0.03, average cluster size of 30, the modified figure is 1309 leading to 44 practices to be recruited. Erring on the side of caution and adjusting for 25% non-response to the baseline questionnaire, 1745 patients will need to be screened and contacted; equivalent to approximately 40 patients per practice. Evidence suggests a consultation rate for OA and peripheral joint pain is at least 15 per month per typical GP practice, suggesting that the template will need to be active for approximately three months at each GP practice. If this poses logistical challenges, reducing the power to an acceptable 80% would result in 980 patients needed to be recruited from 34 practices with clusters of 30 patients (or 1307 to be screened and contacted across the 34 practices to allow for 25% non-response). The run-in period will further inform the estimate of non-response to the baseline questionnaire and if nescessary allow us modify the adjusted sample size needed.

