***Run-in period***

An internal pilot of the trial protocol will take place in four practices, two in each arm. This “run-in” period will be used to ensure that our methods and key assumptions outlined in this protocol work successfully and that the day-to-day administration of the trial runs smoothly. Particular attention will be paid to the recruitment of GP practices, completion rate of the screening template, response rate to, and completion rate of the baseline postal questionnaire and the consent rate to further contact and medical record review. This phase of the trial will run until recruitment at these four practices is complete, which we anticipate to take three months. The template will not be activated in any further practices until this run-in period is complete. Data collected during this phase of the trial will be included in final data analysis as no interim analysis will be carried out with this data. Data from this phase of the trial will only be excluded from the final analysis if any substantial amendments to the current protocol have to be made.

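### The contact target and its run-in revision allow for questionnaire non-response only, although the protocol treats responders who refuse consent as a separate group who cannot be enrolled

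*Protocol*

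**What the plan says.** The Sample size section of the protocol derives 350 patients per arm, inflates for clustering to 1309 in 44 practices, and then sets the mailing target: "adjusting for 25% non-response to the baseline questionnaire, 1745 patients will need to be screened and contacted". The 80% power fallback follows the same route, from 980 recruited to 1307 contacted in 34 practices, again with 25% for non-response. The section then says: "The run-in period will further inform the estimate of non-response to the baseline questionnaire", and that the adjusted sample size may be modified if needed.

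Other sections separate reply from consent:

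- **Study participants, inclusion criteria:** "Provided full written informed consent to study participation and to further contact".
- **Mailing procedure:** a patient who has not replied by 8 weeks is a non-responder. A patient who replies but declines further contact "will also be recorded in the database as a non-consenting responder" and is not approached again. Follow-up questionnaires go only to those who both return the baseline questionnaire and consent.
- **Run-in period:** response to the baseline questionnaire is one item to be watched, and "the consent rate to further contact and medical record review" is another.

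**The concern.** The power calculation needs enrolled patients with follow-up data, because the effect is defined after baseline: "we will think of the effect size as an average of 0.2 over the three follow up time points". A responder who refuses further contact contributes no follow-up measurement. If the 25% covers only people who do not reply, nothing in the contact figure allows for people who reply and refuse.

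The revision rule has the same gap. Suppose the run-in practices show exactly 75% response. On the stated rule 1745 would need no change, yet the number enrolled would be below 1309 unless every responder consented. The consent rate is to be collected, but the Sample size section does not connect it to the contact figure. At stake are the accuracy of the recruitment target and a few points of power.

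**Working it through.** **Inputs, all from the Sample size section:** "Using ρ=0.5 as an estimate of the autocorrelation"; "n=3, Δ=0.2, α=0.05, β=0.10, gives 350 per arm"; icc 0.03; average cluster size 30; 44 practices; 25% non-response. The fallback has 34 practices, 980 recruited and 1307 contacted. The consent rate among responders, c, is not given. I assume 95%, 90% and 80%, that is, 5% to 20% refusal.

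**1. The plan's own figures**

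- Per arm, two-sided α: M = 2(1.960 + 1.2816)² × {1 + (3 − 1) × 0.5} / (3 × 0.2²) = 350.2. Stated: 350.
- Design effect: 1 + (30 − 1) × 0.03 = 1.87.
- Total: 2 × 350 × 1.87 = 1309. Stated: 1309.
- Practices: 1309 / 30 = 43.6, so 44.
- Contacts: 1309 / 0.75 = 1745.3. Stated: 1745.
- Fallback contacts: 980 / 0.75 = 1306.7. Stated: 1307.

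Everything reproduces. Working back, 1745 × 0.75 = 1308.75 and 1307 × 0.75 = 980.25, so non-response alone uses up the whole allowance.

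**2. Enrolment and power if contacts stay as stated**

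- Enrolled: E = contacts × 0.75 × c.
- Cluster size: m = E / practices.
- Design effect: D = 1 + (m − 1) × 0.03, recomputed because clusters shrink while the number of practices is held.
- Variance of the time-averaged difference in SD units: SE² = 2 × (2/3) × D / (E/2).
- Power = Φ(0.2/SE − 1.96).

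Example, main design, c = 0.90: E = 1745 × 0.75 × 0.90 = 1178; m = 26.8; D = 1.773; SE = 0.0634; power = 88.4%.

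| Consent among responders | Main: enrolled | Main: power | Fallback: enrolled | Fallback: power |
|---|---|---|---|---|
| 100% | 1309 | 90.1% | 980 | 80.8% |
| 95% | 1243 | 89.3% | 931 | 79.7% |
| 90% | 1178 | 88.4% | 882 | 78.6% |
| 80% | 1047 | 86.3% | 784 | 75.8% |

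The 100% row lies slightly above the nominal 90% and 80% because the practice counts are rounded up, which makes average clusters a little smaller than 30.

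**3. Contacts needed to enrol 1309**

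Contacts = 1309 / (0.75 × c), and per practice that figure divided by 44:

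| Consent among responders | Contacts | Per practice |
|---|---|---|
| 95% | 1837 | 42 |
| 90% | 1939 | 44 |
| 80% | 2182 | 50 |

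The plan states about 40 per practice.

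**The case against.** A reader might infer that the protocol contains an arithmetic error, or that it counts refusers as enrolled and will certainly miss 1309 and its stated power. The documents do not support that:

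- **The arithmetic is right.** Both divisions reproduce.
- **A looser reading is possible.** The fallback sentence sets 980 recruited against 1307 contacted with 25% non-response as the only step between them, and the allowance is introduced as cautious. The consent form travels inside the baseline questionnaire, so the authors may have meant a usable, consented reply. The non-consenting responder label appears in the mailing section, where its purpose is to prevent further contact.
- **No refusal rate is given.** The lower end of the range above is an assumption.
- **1745 is a planning figure, not a cap.** All eligible patients are mailed while the template is active. At 15 consultations a month, three months in 44 practices gives 15 × 3 × 44 = 1980, more than the 1837 or 1939 needed at 95% or 90% consent.
- **The run-in does watch consent**, and the oversight committees may intervene.

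Most of this stands and limits the point. Two things remain. The looser reading is possible as intent, but the allowance as worded names non-response to the questionnaire, and the Mailing procedure and Run-in period sections keep that apart from consent. And the 1980 is available only if every consulter is eligible, has a completed template and is mailed; the protocol itself expects exclusions and uncompleted templates, and 1980 would not cover 80% consent.

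**Conclusion.** The point holds as a mis-specified allowance and revision rule. Taken literally, 1745 contacts produce 1309 responders, and the number of participants is lower at any refusal rate above zero; the fallback behaves the same way. The size depends on a refusal rate that the documents do not give. Under an assumed 5% to 20%, with 75% response and the number of practices held, main-design power falls to about 89% to 86%, still above the 80% that the protocol calls acceptable. The fallback has less room: about 80% to 76%.

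The revision rule is the more useful part to correct, because a run-in that confirmed the response rate would not, on the stated rule, reveal a shortfall from refusal. These calculations concern losses before enrolment only; loss at 3, 6 and 12 months is a separate matter and is not included.

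**What to change.** In the Sample size section of the protocol:

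1. State that the 25% is a combined allowance for non-response and non-consent. The 1745 and 1307 can then stand. If the 25% is meant as non-response only, restate contacts as 1309 / (response rate × consent rate), give the assumed consent rate, and treat the 980 in the same way.
2. Have the run-in revise the contact figure from the consenting yield: consenting participants divided by patients mailed.

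The cost is a sentence or two and possibly one recalculated figure. The run-in already collects what the yield needs, and the enrolment target of 1309 does not change. The only downside is that the stated contact number may be larger.

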# *Statistical analysis*

Both the primary and secondary analysis will be by intention to treat and appropriate multiple imputation techniques will be used to account for missing data. The primary outcome, the current pain intensity component (0-10 numerical rating scale) of the Chronic Pain Grade [48], will be treated as interval in nature. Multilevel linear mixed modelling will be used to account for the clustered nature of the data. Using treatment by group interaction terms, differences in the mean response profiles will be investigated and quantified using appropriate 95% confidence intervals for the differences between intercept and gradient estimates.

Standard goodness of fit tests will be applied and if the distribution of the residuals is markedly non-normal, bootstrapping will be considered. Time varying covariates can also be accommodated within the multilevel framework.

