## Primary objective

The primary objective of the trial is to determine whether screening for generalised anxiety and depressive symptoms in patients who consult their GP with OA or peripheral joint pain results in an improvement in their pain-related outcomes. Specifically, we hypothesise that patients who are screened for depressive and anxiety symptoms in their GP consultation will have an improvement in their self-reported current pain intensity and pain interference with daily activity ratings (numerical rating scale 0-10) over the 12 months following their consultation, compared to patients in the control arm. Growth curve models will be used to summarise the pattern of response over time between the groups. Changes in slope and intercept will reflect differences in rate of change and mean scores over the 12 months.

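### The 90% power belongs to a time-averaged difference, but the analysis section reports intercept and gradient differences and never names that contrast

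*Protocol*

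**What the plan says.** The Sample size section states its target: "we have considered the sample size needed to estimate the time-averaged difference in the pain response between the two arms". It then fixes the effect: "Given that the mean difference is expected to be zero at baseline, we will think of the effect size as an average of 0.2", over three follow-up points. The calculation is: "Using ρ=0.5 as an estimate of the autocorrelation, n=3, Δ=0.2, α=0.05, β=0.10, gives 350 per arm". With a design effect of 1.87 this becomes 1309 patients in 44 practices.

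The Statistical analysis section specifies a multilevel linear mixed model for current pain intensity and describes the comparison differently: "Using treatment by group interaction terms, differences in the mean response profiles will be investigated", and these are to be "quantified using appropriate 95% confidence intervals for the differences between intercept and gradient estimates". The time-averaged difference is not mentioned there. Neither the time origin nor the role of baseline (outcome or covariate) is stated.

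The Primary objective also refers to growth curves and adds an interpretation: "Changes in slope and intercept will reflect differences in rate of change and mean scores over the 12 months". Table 2 lists current pain intensity at baseline as well as at 3, 6 and 12 months.

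**The concern.** The quantity that was powered and the quantities to be reported are different parameters. A time-averaged difference is one number. An intercept and a gradient are two, and what the intercept means depends on where time zero is placed. If time runs from the index consultation, the intercept difference is the month-0 difference, which the Sample size section expects to be zero. If the benefit is reached by month 3 and then held, the gradient difference over follow-up is zero.

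The trial could therefore produce exactly the effect it was sized for while one of its reported parameters shows little or nothing. How clearly the effect appears would depend on time coding, on whether baseline enters as an outcome, and on the shape of the trajectory. If these choices are still open when the data are seen, they can influence the conclusion.

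The model term is also wrong as written. In a two-arm trial *treatment* and *group* are the same factor, so they cannot interact. A gradient difference comes from group by time.

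**Working it through.** **Inputs (Sample size section):** Δ = 0.2 SD, n = 3, ρ = 0.5, α = 0.05, power 0.90, ICC 0.03, cluster size 30. Follow-up times are 3, 6 and 12 months (Mailing procedure).

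**1. The plan's own figure.** M = 2(z_α + z_β)²{1 + (n − 1)ρ}/(nΔ²) = 2(1.96 + 1.2816)² × 2/(3 × 0.04) = 350.2 per arm. A two-sided α is needed to reproduce it; one-sided gives 285. The design effect is 1 + 29 × 0.03 = 1.87, and 2 × 350 × 1.87 = 1309. Then 1309/30 = 43.6, so 44 practices, and 1309/0.75 = 1745 to be contacted. The arithmetic is right for the time-averaged difference.

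**2. Variances of the other parameters.** Assume unit SD, compound symmetry with ρ = 0.5, complete follow-up, and 350 effective patients per arm (1309/2/1.87). The model is linear in time, and SE = √(2 × variance/350).

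Follow-ups only: mean time (3 + 6 + 12)/3 = 7, sum of squared deviations 16 + 1 + 25 = 42.
- Gradient: variance 0.5/42 = 0.0119, SE 0.00825.
- Intercept centred at month 7: variance 2/3, SE 0.0617. This is the powered contrast: 0.2/0.0617 gives 90.0%.
- Intercept at month 0: variance 2/3 + 49 × 0.0119 = 1.25, SE 0.0845.

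Baseline also an outcome: mean time 5.25, sum of squares 78.75.
- Gradient: variance 0.5/78.75 = 0.00635, SE 0.00602.
- Intercept centred at 5.25: variance 2.5/4 = 0.625, SE 0.0598.
- Intercept at month 0: variance 0.625 + 27.5625 × 0.00635 = 0.80, SE 0.0676.

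**3. Power (two-sided 5%).** The protocol gives only the average effect, so the trajectories are illustrative. Each averages 0.2 SD over the three follow-ups.

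| Difference at 3, 6, 12 months | Outcomes in model | Gradient | Month-0 intercept | Centred intercept |
| --- | --- | --- | --- | --- |
| Constant: 0.2, 0.2, 0.2 | Follow-ups only | 5% | 66% | 90% |
| Linear: 0.086, 0.171, 0.343 | Follow-ups only | 93% | 5% | 90% |
| Fading: 0.3, 0.2, 0.1 | Follow-ups only | 74% (towards lost benefit) | 98.5% | 90% |
| Constant, zero at baseline | Baseline and follow-ups | 60% | 22% | 71% |
| Linear, zero at baseline | Baseline and follow-ups | 99.7% | 5% | 71% |
| Fading, zero at baseline | Baseline and follow-ups | 6% | 54% | 71% |

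Example (row 1, month-0 intercept): z = 0.2/0.0845 = 2.37, power Φ(2.37 − 1.96) = 66%. Example (row 4): the fitted gradient is 0.2 × 5.25/78.75 = 0.0133, z = 0.0133/0.00602 = 2.21, power 60%. The centred intercept there estimates (0 + 0.2 + 0.2 + 0.2)/4 = 0.15, because the zero at baseline dilutes it, and z = 0.15/0.0598 = 2.51 gives 71%.

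**4. Cost of powering a different parameter.** For 90% power on a 0.2 SD month-0 intercept from the follow-ups alone: 2 × 10.507 × 1.25/0.04 = 656.7 per arm, and 2 × 656.7 × 1.87 = about 2456 patients instead of 1309.

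**The case against.** The strongest reply is that the Primary objective pairs slope with rate of change and intercept with mean scores over the year. With time centred on the follow-ups, the intercept difference is the time-averaged difference and has exactly 90% power for every trajectory tried. Time coding is ordinary SAP content. This part stands: a reader might infer that the 90% belongs to neither reported parameter, and the protocol does not support so absolute a claim. What remains is that the reading needs two conditions the protocol does not give (centring at month 7, baseline not an outcome), and that the analysis section itself names intercept and gradient, not the powered contrast.

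A reader might also infer that success could be claimed on either parameter at 5%, with an inflated false-positive rate. The protocol states no such rule. It says that profile differences will be investigated and quantified with confidence intervals, so no multiplicity charge follows.

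The 5% for the gradient under a constant effect is true by construction. It shows that the gradient is not the powered quantity. It does not show that the trial would miss its effect, since the intercept is reported beside it.

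The figures also depend on how clustering is handled. If the practice effect is constant over time it cancels from the gradient, and the 60% becomes 86%. Under that model the time-averaged contrast itself has only about 83%, so the table keeps to the protocol's uniform design effect.

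The interaction term is evidently a slip for group by time, and adds little to the weight of the point.

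**Conclusion.** The point holds as a conflict between the Sample size and Statistical analysis sections. The stated 90% is correct for the difference averaged over 3, 6 and 12 months. At the same 1309 patients, power ranges from 5% to over 99% for the gradient and from 5% to 98.5% for a month-0 intercept, across trajectories that all average 0.2 SD. An intercept centred on the three follow-ups keeps the 90%; modelling baseline as an outcome and centring over all four times lowers it to 71%. These figures assume compound symmetry with ρ = 0.5, complete data, the 1.87 design effect applied to every contrast, and illustrative trajectories.

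The sample size is not wrong, and the stated model can deliver the powered contrast. The correction is one of alignment and does not call the design into question, but it should be made before the outcome data are analysed.

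**What to change.** In Statistical analysis, name one primary contrast: the between-arm difference in mean current pain intensity averaged over 3, 6 and 12 months, with its 95% confidence interval, from the mixed model with patient and practice random effects. Fit time as a factor and average the three follow-up differences. If time is linear, centre it at month 7 and state that baseline is not an outcome in the model. Replace *treatment by group* with *group by time*, and make that interaction and the gradient difference secondary. Reword the Primary objective so that the mean difference over follow-up is the decisive quantity and the rate of change is supportive.

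The alternative is to keep the intercept or gradient as primary and recompute the power for it under a stated time origin and trajectory.

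The first option costs a few sentences and no extra data or patients. Its downside is that the gradient becomes a secondary result.

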***Recruitment procedure***

*GP Practices*

Approximately 44 “Research Ready” GP practices that use the EMIS consultation system will be recruited through West Midlands Primary Care Research Network (PCRN) (North Cluster). Information given to practices will be general and they will be told that both arms of the trial will ask some questions that are not unlike those already asked as part of best practice primary care, e.g. assessment of pain intensity and depressive symptoms. Information divulged prior to randomisation will be minimal in order to reduce any bias in the practice deciding to take part as they will be told that they have an equal chance of being allocated to either the control or intervention arm. Practices will be selected on the basis of recent research activity, practice demographics and willingness to participate in the study. The GP practices involved in the study will include those from both urban and rural areas, different socio-economic groups and all sizes of practice (based on patient list size and number of GP partners).

When a practice has agreed to take part in the study, the set-up procedure in the practice will involve downloading anonymised patient information on consultation rates for OA, depression, anxiety, and the comorbid rates of these symptoms. An audit of access to psychological services will also be carried out to ensure that they have the resources to run the study adequately. Details of how practices will be randomised to the trial arms and the post-randomisation procedure are given below.

It is anticipated that the template will be active in each GP practice for approximately three months. GP practices will not all be recruited at once, rather recruitment will take place over a one year period and so the template will not be active in all practices at any one time. A service-level agreement will be ascertained with each GP practice, with a small reimbursement included to pay for practice time

*Patients*

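### Intercept and gradient differences, read as one straight line per arm that includes baseline, understate the powered follow-up average when the effect plateaus or wanes

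*Protocol*

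**What the plan says.** Three parts of the protocol bear on this.

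- **Statistical analysis.** A multilevel linear mixed model is planned for pain intensity. Differences between the arms' mean response profiles are to be quantified by "95% confidence intervals for the differences between intercept and gradient estimates".
- **Primary objective.** Growth curve models are to be used, and "Changes in slope and intercept will reflect differences in rate of change and mean scores over the 12 months".
- **Sample size.** The calculation targets the time-averaged difference and takes the arms to be level at the start: "we will think of the effect size as an average of 0.2 over the three follow up time points". It uses three repeated measures, which are the follow-ups without baseline.

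Table 2 shows the primary outcome collected at baseline and at 3, 6 and 12 months. The protocol does not say where time zero lies, whether time is centred, whether it enters as a straight line, or whether baseline pain is a response or a covariate. It also does not say what course the effect is expected to take between 3 and 12 months.

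**The concern.** One intercept and one gradient per arm describe a straight line. If baseline is one of the points on that line, the arm difference has to change at a constant rate from month 0 to month 12. A difference that is zero at baseline and 0.2 SD on average afterwards fits such a line only if benefit grows in proportion to time. The intervention is a prompt at a single consultation, so an effect that is present by 3 months and then holds or fades is at least as easy to imagine.

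For those shapes the fitted line places part of the benefit at month 0, where the plan expects none, and lowers the fitted average over follow-up. The quantity for which the trial was sized would then be estimated with bias and tested with less than the planned power. The gradient, one of the two named summaries, could be close to zero despite a benefit of the planned size.

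**Working it through.** **The plan's own figure.** The stated inputs are "Using ρ=0.5 as an estimate of the autocorrelation, n=3, Δ=0.2, α=0.05, β=0.10, gives 350 per arm". With two-sided α:

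M = 2(1.960 + 1.282)²{1 + 2 × 0.5}/(3 × 0.2²) = 350 per arm.

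The design effect is 1 + 29 × 0.03 = 1.87, and 2 × 350 × 1.87 = 1309, which at 30 per practice gives 44 practices. The sample size reproduces. It is the size for the mean of the three follow-up differences.

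**Fitting the line.** Assume baseline is a response, time is in months, and the two arms have free intercepts and gradients. With complete data and equal correlation of 0.5 between visits, the fitted arm difference is the least-squares line.

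- Times are 0, 3, 6 and 12, with mean 5.25.
- Deviations are −5.25, −2.25, 0.75 and 6.75, with sum of squares 78.75.
- Any profile with zero at baseline and a follow-up mean of 0.2 has a four-visit mean of 0.6/4 = 0.15.
- The follow-up visits average 7 months, so the fitted follow-up average is 0.15 + (7 − 5.25) × gradient = 0.15 + 1.75 × gradient.
- This equals 0.2 only when the gradient is 0.0286 per month. Growth in proportion to time gives that gradient (0.086, 0.171, 0.343 SD).

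**Power of the fitted average.** Use the effective 350 per arm (1309/2 divided by 1.87).

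- Variance of the difference in four-visit means: 2(0.5 + 0.5/4)/350 = 0.003571.
- Variance of the gradient difference: 2 × 0.5/(78.75 × 350) = 0.0000363.
- Standard error of the fitted follow-up average: √(0.003571 + 1.75² × 0.0000363) = 0.0607.
- For comparison, the plain mean of the three follow-up differences has standard error √{2(0.5 + 0.5/3)/350} = 0.0617. Then 0.2/0.0617 = 3.24, which gives the planned 90%.

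**Results** (assumed profiles in SD at 3, 6 and 12 months, each averaging 0.2):

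| Profile | Gradient per month | Fitted month-0 difference | Fitted follow-up average | Power for that average |
|---|---|---|---|---|
| 0.2, 0.2, 0.2 | 1.05/78.75 = 0.0133 | 0.15 − 0.07 = 0.08 | 0.173 (13% low) | 81% |
| 0.3, 0.2, 0.1 | 0.15/78.75 = 0.0019 | 0.15 − 0.01 = 0.14 | 0.153 (23% low) | 71% |
| 0.1, 0.2, 0.3 | 1.95/78.75 = 0.0248 | 0.15 − 0.13 = 0.02 | 0.193 (3% low) | 89% |

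For 0.3, 0.2, 0.1 the gradient alone has about 6% power.

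**Sensitivity.**

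- First-order autoregressive correlation, 0.5 between neighbouring visits: the fitted averages fall to 0.153 (constant) and 0.120 (waning).
- Visits coded as equally spaced (0, 1, 2, 3): the averages are 0.15 + 0.5 × 0.06 = 0.18 and 0.15 + 0.5 × 0.02 = 0.16. Most of the shortfall therefore remains without unequal spacing.
- Intercept centred at the mean of all four visits: it reads 0.15 for every profile, because it averages in the zero at baseline.
- Line through the three follow-ups only, centred at 7 months: it reads 0.200 with 90% power for every profile.

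**The case against.** The strongest reply is that the straight line is inferred. The word linear in the model's name describes the model class, and the protocol also speaks of response profiles and patterns over time. The primary objective ties the intercept to mean scores, and the sample size counts only the three follow-ups. Both would fit a line through the follow-ups centred at their mean, which is not biased for the average. Time coding and baseline handling are also commonly left to a statistical analysis plan. This stands as a limit on the claim: the figures hold only with baseline in the line. It does not remove the point, because the protocol does fix which summaries quantify the effect, and these recover the powered quantity only under coding choices it does not make.

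A reader might infer that the average is under-read whichever summary is made primary. The documents do not support that. The centred follow-up line is unbiased, as is a model with baseline as a covariate under equal correlation, and a common-baseline model cannot show a month-0 difference. For a benefit confined to 3 months (0.6, 0, 0), a joint test of intercept and gradient would still have about 93% power. Nor is unequal spacing the main cause, as the equal-spacing figures show.

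The goodness-of-fit checks are a partial safeguard. However, the remedy named with them is bootstrapping for non-normal residuals, which does not correct a wrong mean shape. A fitted month-0 difference need not be taken for imbalance either. Pain is observed directly at the consultation and at baseline, so misfit could be noticed. The baseline questionnaire also follows the consultation, so a real early effect is possible.

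Finally, the effect shapes are assumed. For a sustained step, the 81% power is still above the 80% that the protocol calls acceptable.

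**Conclusion.** The point holds in a limited form. The objective and the analysis section quantify the effect by intercept and gradient, while the sample size section powers the mean of the three follow-up differences with none at baseline. On the natural reading, those summaries do not estimate the powered quantity unless benefit builds up roughly in proportion to time. The cause is a non-linear effect combined with baseline lying on the line.

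The size depends on the shape, which the protocol does not give: 3% low for a steady rise, 13% for a sustained step, and 23% for the waning profile. Power for the fitted average is about 89%, 81% and 71% respectively, against 90% planned. These figures assume complete data, equal correlation of 0.5, the protocol's design effect, and baseline as a response with free intercepts. They show what the stated summaries allow. They do not show that the trial's result will be biased.

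**What to change.** Within the same multilevel model:

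1. Treat time as a factor with arm-by-time terms.
2. State how baseline enters (response or covariate), and which measurement it is. Pain is rated both at the consultation and in the postal questionnaire that follows it.
3. Make the mean of the 3-, 6- and 12-month arm differences the primary estimate, with its 95% confidence interval, and report the three differences beside it.
4. Keep the gradient difference as a descriptive secondary summary, and align the wording of the primary objective.

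Under equal correlation this mean reads 0.200 SD with the planned 90% power for every profile above. Adjusting for baseline, or constraining it to be equal, would raise power to about 98% if the design effect stays at 1.87. The cost is a change of wording and a few extra parameters against about 1,300 patients. No data collection changes.
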